
#### Statistical analysis using YTO Models.

We will employ a YTO model, which provides a more detailed representation of disease-related changes (between 50 and 0 YTO) than an age-based analysis [15,16,18,23]. Our statistical analyses are derived from Langbehn et al. [80] and our own work [17] investigating neural and behavioral changes across YTO. This method is based primarily on data from individuals with CAG repeats between 41 and 56 [80] but extrapolation has generalized usefully to CAG repeats extending beyond this range (40, 57–70, etc.) [17]. Because individuals with between 36–39 CAG repeats represent an incomplete penetrance group, they will be excluded from the YTO analysis and will be examined separately in exploratory analyses. Individuals with >70 CAG repeats will also be excluded as they are likely to have already begun showing motor symptoms of HD and are likely classified as patients with JOHD. All hypotheses relate to either systematic group difference between GE and GNE individuals or to differences within the GE group driven by CAG expansion length and age (or years to onset as in the NfL analysis). Our analysis approach will include the following steps: 1) age and sex correction based on the data from healthy controls, 2), estimation of YTO, and 3) YTO modeling with testing for potential additional sex differences and sex by YTO interactions.

For each dependent variable, we apply statistical corrections to separate developmental effects of typical aging from those experienced by GE individuals as part of the disease trajectory. We perform this correction by modeling age and sex effects in GNE controls using a regression that includes within-subject and within-family random effects. The models incorporate both linear and potential non-linear age relationships. Nonlinearity is modeled flexibly via restricted cubic splines (“natural splines”). The degree of non-linearity (up to five degrees of freedom) is determined by choosing the model with the lowest Akaike Information Criterion (AIC), with tied AIC values (≤ 1.0) favoring the simpler model. We also test the model for sex and sex-by-age interactions, which are excluded from the final model if found to be nonsignificant. The fitted values for this model are then subtracted from the dependent value to complete the correction.

Estimation of age of motor symptom onset is calculated using the Langbehn model [80] shown below:

$$\begin{array}{c} Age\;of\;motor\;symptom\;onset=\text{2}\text{1}.\text{5}\text{4}-(\text{9}.\text{5}\text{5}\text{6}-\text{0}.\text{1}\text{4}\text{6}*CAG) \end{array}$$

YTO is then calculated by simply subtracting participants’ ages (in years) from age of motor symptom onset. (The abbreviation YTO, now established by precedent, stands for a slight misnomer. The value is the number of years from the mean age of onset for those with the given CAG length. It is not the individual’s number of years to onset—which is unknowable—and is slightly different from the individual’s expected years to onset, given that they have reached their current age without already experiencing onset.)

A limitation of this YTO approach is that it can only approximate the relationship between true years to HD onset and the outcome measures. As noted earlier, the YTO calculations are slightly biased estimates of participants’ expected years to onset. Furthermore, a person’s true years to onset has a probability distribution around the CAG-specific average. For concave relationships, such as those we typically expect in the neurodevelopment of brain volumes, substitution of an average value for a probability distribution causes at least slight underestimation of the predicted value that would be obtained from a model based on the true (but unknowable) number of years from onset (Jensen’s inequality).

We assess the relationship between YTO and age- and sex-adjusted outcome measures in GE individuals using an additional mixed effects regression, again including random effects for repeated measures of the same participant and for similarities between participants from the same family. Similar to the GNE model described above, the potentially nonlinear influence of YTO is modeled using restricted cubic splines with degrees-of-freedom chosen by AIC. Sex and sex interactions with YTO are tested and included in the model if significant. The mixed effect models are fitted by maximum likelihood and F-test degrees of freedom are estimated using the Satterthwaite approximation. The summary of the resulting model indicates a p-value for the effect of YTO, which, if significant, indicates a statistically meaningful difference of GE from GNE along the YTO trajectory. Finally, we plot these relationships and their 95% confidence intervals to determine where these differences occur along the trajectory (50−0 YTO)

To assess the relationship between age- and sex-adjusted neuroimaging variables (e.g., cortical grey and white matter volume, striatal volume, corticostriatal structural and functional connectivity, etc.) and clinical outcomes in GE individuals, we apply modeling techniques as described above. The models include random effects of subject and family, but exclude age and sex, as the values will have already been corrected using the data from GNE participants. Imaging measures are generally predictor variables, and clinical measures are the outcomes, reflecting the potential causal relationships between the two measurement classes. As in our previous work [17], we also split our GE participants into two groups with a cutoff of 20 YTO and test for differences in the imaging versus clinical relationships. This is based empirically on our work [17] showing divergence in neural and behavioral measures at this point in the YTO trajectory and because of work showing an upward trend in NfL at 20 YTO [18]. As described above, potential non-linear relationships between biomarkers and clinical measures are interrogated using restricted cubic splines (up to five degrees of freedom). For all analyses, a *p* value of < 0.05 is considered statistically significant.

In addition to our hypothesis-driven analyses, we also plan to perform detailed exploratory analyses to uncover novel neuroimaging biomarkers that both distinguish GE and GNE individuals and individuals with variations in HD-related single nucleotide polymorphisms (SNPs). For example, machine learning approaches, such as deep learning, have been applied to neuroimaging data from patients with neurodegenerative disorders to identify how those SNPs affect brain anatomy and function [81]. As mentioned above, SNPs in several genes explain variation in the eventual onset of motor symptoms in HD [32–34]. Using deep learning and other machine learning approaches as exploratory tools may reveal new mechanistic information about how these SNPs shape neurodevelopment and -degeneration.

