#### Magnetic resonance imaging.

Our main goal in designing the ChANGE-HD MRI protocol was to improve on the Kids-HD protocol, giving us the best chance of reproducing previous findings [17] and revealing new ones. To this end, the MRI protocol was designed to collect high resolution structural and functional MRI data within the time span of a typical research MR exam (~1 hour). To harmonize data across scanning sites, the scanning protocol was adapted from the ABCD study [31]. We used 3 Tesla research scanners to collect T1-, T2-, and diffusion-weighted, and resting-state functional MR brain images (see Table 7 for sequence parameter details). These sequences have been adapted and optimized for all six sites across Philips, General Electric, and Siemens MR scanner platforms.

**Table 7 pone.0336088.t007:** ChANGE-HD harmonized imaging scanning parameters for 3T scanners. FOV = field of view, TR = repetition time, TE = echo time, TI = inversion time, MP = MPRAGE, GR = spoiled gradient echo. VUMC = Vanderbilt University Medical Center.

Siemens (CHOP/ UC Davis)	Matrix	FOV	%FOV phase	Resolution (mm)	TR (ms)	TE (ms)	TI (ms)	Flip Angle (deg)	Parallel Imaging	Multiband Acceleration	Phase partial Fourier	b-values	Acquisition Time
**T1**	256x256x176	256x256	100	1.0x1.0x1.0	2500 (MP)	2.90	1060	8	2x	Off	Off	N/A	7:26/ 5:48
**T2**	256x256x176	256x256	100	1.0x1.0x1.0	3200	564/545	N/A	120/ Var	2x	Off	Off	N/A	4:52/ 4:42
**Diffusion**	140x140x81/ 122x122x78	240x240/ 241x241	100	1.7x1.7x1.7\ 2.0x2.0x2.0	4100/ 4170	88/ 103	N/A	88/ 90	Off	3	6/8	**CHOP**: 500 (6), 1000 (20), 2000 (20), 3000 (64). **UC Davis**: 500(6), 1000(15), 2000(60)	13:57/ 7:05
**fMRI**	90x90x60/ 86x86x60	216 x 216	100	2.4x2.4x2.4	800	30	N/A	52/67	Off	6	Off	N/A	5:00 x 4/ 4:08 x 4
Philips (**UT Houston**/ **VUMC**)	Matrix	**FOV**	**%FOV phase**	**Resolution (mm)**	**TR (ms)**	**TE (ms)**	**TI (ms)**	**Flip Angle (deg)**	**Parallel Imaging**	**Multiband Acceleration**	**Half Scan Factor**	**b-values**	**Acquisition Time**
**T1**	256x256x225	256x256/ 256x240	93.75	1.0x1.0x1.0	6 (GR)	3.0	1060	8	2 x	Off	Off	N/A	5:52
**T2**	256x256x256	256x256	100	1.0x1.0x1.0	2500	251.7/ 268	N/A	90	2.5 x	Off	Off	N/A	2:53/ 2:50
**Diffusion**	144x144x80	240x 240	100	1.7x1.7x1.7	6500	96	N/A	78	Off	3/ 4	0.603	500 (6) 1000 (15) 2000 (15) 3000 (60)	11:07/ 11:11
**fMRI**	96x96x60	230x230	100	2.25x2.25x2.4	800	30	N/A	52	Off	6	Off	N/A	5:00 x 4/ 5:15 x 4

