General Electric (**Iowa**/ **Columbia**)	Matrix	**FOV**	**%FOV phase**	**Resolution (mm)**	**TR (ms)**	**TE (ms)**	**TI (ms)**	**Flip Angle (deg)**	**Parallel Imaging**	**Multiband Acceleration**	**Phase partial Fourier**	**b-values**	**Acquisition Time**
**T1**	256x256x208	256x256	100	1.0x1.0x1.0	2622 (MP)/ 2296 (MP)	2.96	1060	8	2 x	Off	Off	N/A	7:12/ 7:20
**T2**	256x256x208\ 256x256x204	256x256	100	1.0x1.0x1.0	3200/3202	60/ 55.7	N/A	Var/ 90	Off	Off	Off	N/A	6:28/ 4:58
**Diffusion**	140x140x81	240x240	100	1.7x1.7x1.7	9000/ 10000	102 \ 101.7	N/A	90	Off	2	5.5/8/ Off	**Iowa**: 500(6) 1000(15) 2000(15) 3000(60) **Columbia:** 3000 (96)	14:36/ 17:30
**fMRI**	96x96x60	307x307	100	2.4x2.4x2.4	800	30	N/A	52	Off	4/ Off	Off	N/A	5.00 x 4

As in the ABCD study, all images across sites were acquired in the axial plane because GE and Philips scanners may cause ghosting artifacts when acquired at oblique angles. Several improvements have been made to our MRI protocol since the Kids-HD study. While Kids-HD involved a single Siemens scanner at the University of Iowa, ChANGE-HD involves a mix of three vendors (Iowa: General Electric, CHOP: Siemens, Columbia: General Electric, UT Houston: Philips, UC Davis, Siemens, Vanderbilt: Philips). T1- and T2-weighted scan resolution has been increased by decreasing voxel sizes from 1.1 mm (T1) and 1.0x1.4x1.0 mm (T2) to 1.0 mm isotropic. To improve signal-to-noise ratio (SNR), we also increased the head coil channels from 12 in Kids-HD to between 32 and 48 (depending on scanner model) in ChANGE-HD.

Several improvements to resting-state functional scans were made. First, instead of acquiring one five-minute scan, we collected two scans (10 minutes total), each with opposite phase encoding directions. These improvements were made to reduce the effects of spurious noise and improve SNR [66], while reducing susceptibility effects [67]. Voxel and temporal resolution were also improved by decreasing voxel size from 3.4x3.4x4.0 mm to at least 2.4 mm isotropic and decreasing the TR from 2500 ms to 800 ms, respectively.

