Finally, diffusion scanning was improved by decreasing voxel sizes from 2.0 to 1.7 mm isotropic and reducing distortion potential by lowering the echo time from 81 ms in Kids-HD to 69 ms in ChANGE-HD. Thus, the improvements in hardware and software represent a significant technological improvement between studies. Although scanning times differed by study site and participant visit, the approximate active scanning time was ~ 1 hour, including ~16 minutes for structural T1/T2 scans, ~ 18 minutes for diffusion scans, ~ 22 minutes for resting state scans, and ~2 minutes for BOLD field maps. Participants were given opportunities to take breaks and leave the bore, if needed.

During data collection periods, several quality control measures were followed to optimize scan quality. First, prior to study initiation, and once per year, each site was responsible for human phantom calibration. These calibrations were performed by designated credentialed imaging experts at each site (see S1 Table for each imaging expert). Second, each site’s imaging expert and team were required to regularly check scans for signs of poor scan quality, such as low tSNR or high resting state scan motion. In some cases, scans were repeated to ensure high image quality (e.g., the appearance of participant motion during resting state scanning). Third, deviations in protocol or changes to the study MRI system were noted by each site’s MR physicist. Post-data collection metrics of quality control will be reviewed to ensure that our final scans include only those with SNR of above 20, 45, 25, and 10 for anatomical, resting-state, b0, and b1000 diffusion scans, respectively. Resting state functional scans will be rejected if average framewise displacement exceeds 0.3 mm and frames will be censored if motion exceeds 0.3 mm.

All raw (uncensored, uncorrected, etc.) neuroimaging data collected under this protocol will be de-identified and uploaded to the NDA following data collection and analysis. Structural MRIs will be defaced to prevent participant identification.

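### The imaging models have no site or scanner term, although the study pools six sites and three vendors; unremoved scanner offsets cost precision, and Columbia's diffusion entry needs reconciling

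*Protocol article*

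**What the plan says.** The section on statistical analysis using YTO models lays out three steps: "1) age and sex correction based on the data from healthy controls, 2), estimation of YTO, and 3) YTO modeling". The first step is fitted in gene-non-expanded (GNE) participants by "modeling age and sex effects in GNE controls using a regression that includes within-subject and within-family random effects". The second regression, of the corrected outcomes on YTO in GE participants, is described as "again including random effects for repeated measures of the same participant and for similarities between participants from the same family". For the imaging-clinical analyses: "The models include random effects of subject and family, but exclude age and sex". Spline selection by AIC, maximum likelihood fitting and Satterthwaite degrees of freedom are also specified. Site, scanner and vendor appear in none of these models, and no statistical harmonisation step is described.

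The MRI section says of the hardware: "While Kids-HD involved a single Siemens scanner at the University of Iowa, ChANGE-HD involves a mix of three vendors". It also states measures on the acquisition side: "To harmonize data across scanning sites, the scanning protocol was adapted from the ABCD study"; "prior to study initiation, and once per year, each site was responsible for human phantom calibration"; and thresholds so that "final scans include only those with SNR of above 20, 45, 25, and 10 for anatomical, resting-state, b0, and b1000 diffusion scans, respectively". The MRI processing section adds common containerised pipelines for all sites.

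**The concern.** The stated analysis derives partly from the group's Kids-HD work, where one scanner made a scanner term unnecessary. That condition no longer holds. A stable scanner offset shifts every visit of a participant who stays at one site. The subject and family random effects absorb the shift as extra between-person variance; they do not remove it. Subtracting the GNE fit does not remove it either, because that fit is pooled over sites. In an accelerated longitudinal design, much of the information on YTO comes from comparing different people, so this variance falls on the comparison of interest.

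Two things are at stake. The first is precision: the power figures come from single-scanner data and contain no between-scanner variance. The second is validity: if sites differ in the YTO of their GE participants, or in their GE to GNE mix, scanner offsets enter the fitted curve. Diffusion raises a further question, since Table 7 lists b-value schemes that differ between sites.

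**Working it through.** **1. Spread over scanners.** Table 4 totals 1,004, which I read as visits because the matching target is 1,030 assessments. General Electric sites: 302 + 119 = 421. Siemens: 187 + 112 = 299. Philips: 153 + 131 = 284. No vendor dominates. Vanderbilt's counts start in 2024, so site is also tied to calendar time.

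**2. The plan's own power figures.** Inputs from the power section and Table 5: 180 planned and 79 source GE participants, alpha 0.01. Projected F = F × 180/79 = F × 2.278. NCP = (F − 2F/ddf − 1) × ndf, with ddf also multiplied by 2.278. Power comes from the noncentral F distribution.
- Thalamus: 7.47 × 2.278 = 17.02 (printed 17.03); NCP about 15.88 (printed 15.871); power 0.916, as printed.
- Curvature: 10.49 × 2.278 = 23.90 (printed 23.92); NCP about 22.57 (printed 22.559); power 0.983, as printed.

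Table 5 therefore reproduces.

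**3. Adding an unmodelled scanner component.** The article gives no between-scanner variance. Assume a between-site SD equal to s times the within-site SD, with s from 0.3 to 0.5. Variance is multiplied by 1 + s², that is by 1.09 to 1.25. The printed NCP is divided by that factor:

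| Outcome | Printed power | s = 0.3 | s = 0.5 |
|---|---|---|---|
| Thalamus (NCP 15.871 → 14.56, 12.70) | 0.916 | 0.887-0.888 | 0.832 |
| Curvature (22.559 → 20.70, 18.05) | 0.983 | 0.973 | 0.948 |
| Cortical gray matter, primary (26.593 → 24.40, 21.27) | 0.995 | 0.990 | 0.977 |
| Whole brain, primary (49.491 → 45.40, 39.59) | >0.999 | >0.999 | 0.999 |
| Cerebral white matter, primary (63.099 → 57.89, 50.48) | >0.999 | >0.999 | >0.999 |

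The range in the thalamus cell reflects rounding of the NCP. Cortical thickness, also primary, is outside the 90% claim at 0.406. Dividing the full NCP is on the pessimistic side, because within-person change carries no stable site offset.

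**4. Bias against lost precision.** This used a simple cross-sectional simulation: 180 participants, sites in Table 4 proportions, nominal alpha 0.05, scanner share of variance 10-30%.
- No link between site and YTO: type I error without a site term is 0.055-0.060. Power falls from about 0.91 to 0.88-0.82, and a site term restores about 0.90.
- Mean YTO differing between sites by assumed offsets of up to ±0.5 SD: type I error is 0.096-0.169 without the term and 0.054-0.055 with it.

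**5. Acquisition differences in Table 7.**
- T1: listed TR, TE, slice count and acquisition time vary by vendor or site; voxel size, TI and flip angle are common.
- Diffusion, by site:
  - Iowa, UT Houston and Vanderbilt: shells 500, 1000, 2000 and 3000, with 6 + 15 + 15 + 60 = 96 directions, at 1.7 mm.
  - CHOP: the same four shells, with 6 + 20 + 20 + 64 = 110 directions, at 1.7 mm.
  - UC Davis: 500, 1000 and 2000 only, at 2.0 mm.
  - Columbia: the entry reads 3000 (96).

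Read literally, Columbia has one shell and no b1000 data. But 96 is exactly Iowa's total number of directions, and the diffusion analysis paragraph says several b-values are acquired, without exception. The cell may therefore give a maximum b-value and a total. The article does not settle which.

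**The case against.** The strongest reply is that this is a condensed article. Saying that a regression includes certain random effects is not an exhaustive list, and a site covariate could sit in a full plan that is not shown. That limits the point to what the article states. Still, the article does not defer the model: it gives fixed effects, random effects, spline rule, estimation and degrees of freedom for the main models, and it discusses scanner differences elsewhere without carrying them into any of them.

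A second reply is that harmonisation is not neglected: protocol, phantom calibration, quality thresholds and pipelines are all stated. This stands. They reduce offsets at source, but the article describes no use of the phantom data in the analysis and nothing that removes what remains.

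A third concerns size. Thalamus and curvature are starred as neither primary nor secondary outcomes, and the SD ratio is assumed. That also stands. A reader might infer that the study is underpowered; the table above does not support it for the primary outcomes that the 90% claim covers.

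A reader might also infer that the YTO curve is biased. The article reports no site mix by age, CAG length, YTO or gene status, and staff who meet participants are blind to genotype, so selection by gene status at a site is unlikely. Bias is conditional.

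Finally, a reader might conclude that Columbia's 119 of 1,004 visits (11.9%) fall outside the b1000 quality rule and yield fractional anisotropy on another scale. That depends on one reading of a table cell that has a plausible alternative.

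**Conclusion.** The omission is real and worth correcting. As described, the three models leave any residual scanner offset in the between-person variance of every imaging outcome. Under the assumed SD ratio of 0.3 to 0.5, thalamus drops below the claimed 90% (to about 0.89-0.83). Curvature stays above it, as do whole brain, cortical gray matter and cerebral white matter (0.977 or higher). Type I error is at risk only if site is related to YTO or gene status, which cannot be judged from the article.

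On diffusion, two things are firm. UC Davis differs in voxel size and lacks a b=3000 shell. Columbia's entry, taken literally, conflicts with the text on multiple b-values and with the b1000 rule. Non-comparability of Columbia's data is a question to answer, not an established fact.

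**What to change.** Include scanner/site as a factor in the GNE correction, with a new level whenever a scanner changes. Subtract the site-specific fitted values from the GE outcomes, and carry the factor into the GE YTO and imaging-clinical models. Define the plotted GE-GNE curve as an average over sites. Report site mix by YTO and gene status, so that the scope for bias can be seen.

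For diffusion, reconcile Columbia's Table 7 entry with the diffusion paragraph and the b1000 threshold. Compute tensor measures from shells common to the sites: 500, 1000 and 2000 are listed at the other five. If Columbia is truly b=3000 only, it shares no non-zero shell with UC Davis; analyse it separately, with its own quality threshold.

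The cost is about five degrees of freedom per model (six levels; more if scanners change), against roughly 180 GE participants and 400 GE visits in the YTO model, plus at most one extra diffusion analysis. No new data are needed.

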### Power analysis and sample size calculation

Based on our findings from the Kids-HD sample, our central hypothesis is that GE participants will demonstrate altered trajectories in general brain size and cognition across YTO. Specifically, we predicted that GE individuals will demonstrate significantly larger brain volume (primary outcome measure) and stronger cognition scores (secondary outcome measures) prior to 20 YTO and significantly smaller brain volume and weaker cognition between 20−0 YTO. Using our updated recruitment target of 1,030 assessments across 450 participants, we estimated at least 90% power to reproduce our previous findings at p = .01 (except for cortical thickness; Table 5). Note that Table 5, which shows the results of our power analysis, includes functional and structural measures, but that our power analysis is primarily based on the structural findings from Kids-HD. Assuming 40% of participants are GE (as in the previous study), we can assume at least 400 visits from 180 unique genetically affected participants. The power analysis used the Kids-HD sample from Neema et al. (2024), and was based on 136 visits from 79 gene-expanded participants. Because the mean number of visits (and hence, statistical information) per participant will be higher in ChANGE-HD, a conservative estimate of the overall increase in statistical information (i.e., log-likelihood statistics) is obtained from the ratio of unique participants, which is 2.278. If the findings from Kids-HD hold, then the expected values of the analogous F statistics (Table 5) will increase by at least 2.278-fold. Standard power calculations using these projected F statistics yield results that exceed the above-claimed minimum statistical power.

**Table 5 pone.0336088.t005:** Tests used for hypotheses and power analysis (from Neema et al., 2024).

		Kids-HD				Change-HD		
**Measures**	**N**	**ndf**	**ddf**	**F**	**p**	**Projected F**	**Projected NCP**	**Power**
General Ability Index**	136	1	87.66	13.50	<0.001	30.78	29.445	0.997
Behavior composite**	135	2	120.27	10.91	<0.001	24.87	47.343	>0.999
PANESS**	128	1	46.12	8.92	0.005	20.34	18.933	0.956
Whole brain*	117	3	62.63	7.79	<0.001	17.76	49.491	>0.999
Cerebrum	117	3	62.55	7.80	<0.001	17.78	49.557	>0.999
Cortical gray matter*	117	1	99.90	12.22	<0.001	27.86	26.593	0.995
Cortical surface area	117	1	95.22	12.17	<0.001	27.75	26.468	0.994
Cortical thickness*	117	1	54.67	2.95	0.091	6.73	5.612	0.406

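### As described, the test for additional sex differences in GE participants does not compare GE with GNE, and its false-positive rate is above the nominal 5%

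*Protocol article*

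**What the plan says.** All of this stands in the protocol article, under the heading on statistical analysis using YTO models.

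- **Correction in GNE.** Age and sex effects are modelled in GNE controls with subject and family random effects. Sex and sex-by-age interactions are tested, "which are excluded from the final model if found to be nonsignificant". The fitted values are then subtracted from the outcome. The rule applies to every dependent variable.
- **Test in GE.** The third analysis step is described as "YTO modeling with testing for potential additional sex differences and sex by YTO interactions". The later text places this in a second mixed model for GE individuals: "Sex and sex interactions with YTO are tested and included in the model if significant".
- **Threshold.** For all analyses, a p "value of < 0.05 is considered statistically significant".
- **Imaging–clinical models.** These leave out age and sex on the ground that the GNE correction has already dealt with them.

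The article describes no direct GE-versus-GNE comparison of the sex effect, and no step that carries the estimation error of the GNE fit into the GE test.

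**The concern.** Suppose men and women differ on an outcome by the same amount in both groups, so that the expansion plays no part. Two things can then go wrong.

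1. If the difference misses significance in GNE, nothing is subtracted for it. It stays whole in the GE values, where the next test can find it. A result significant in one group and not in the other is then read as a difference between the groups.
2. If the difference is significant in GNE, an estimate of it is subtracted as if it were known. The GE test uses only GE sampling error, so its standard error is too small.

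Either way, an ordinary sex difference can be reported as one that goes beyond normal. The imaging–clinical models inherit the first problem: where a sex term was dropped, the values have not been corrected for it, yet sex is left out as though they had been.

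**Working it through.** **Inputs.**
- Recruitment target: "Using our updated recruitment target of 1,030 assessments across 450 participants".
- GE group: "at least 400 visits from 180 unique genetically affected participants", from an assumed GE share of 40%. GNE is therefore 450 − 180 = 270.
- Threshold 0.05, taken as two-sided (critical value 1.96); the article does not state sidedness.
- Sex split: 177 of 404 (43.8%) male, from the Kids-HD description in the Introduction, carried over as an assumption.
- One effective observation per participant: an assumption.
- True sex difference d, in SD units and equal in GE and GNE: an assumption, shown over a range.

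**The plan's own figures.** The article states no error rate for the sex tests. Its Table 5 power figures use the same 180 GE participants and can be reproduced. The information ratio is 180/79 = 2.278. For the General Ability Index, F = 13.50 × 2.278 = 30.75 and ddf = 87.66 × 2.278 = 199.7, so NCP = 30.75 − 2 × 30.75/199.7 − 1 = 29.445, as stated. Power at 0.01 comes to 0.998 against the stated 0.997. Cortical thickness gives 0.418 against 0.406. The sample-size inputs are thus the plan's own.

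**Standard errors of the sex difference.** With p = 0.438, v = 1/(n·p·(1 − p)).
- GNE: v_N = 1/(270 × 0.2462) = 0.0150, SE 0.123.
- GE: v_E = 1/(180 × 0.2462) = 0.0226, SE 0.150.

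**False-positive rate under the rule.** Let b_N and b_E be the two estimated sex differences, independent and both centred on d.

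Rate = P(dropped) × P(|b_E|/√v_E > 1.96) + P(kept) × P(|b_E − b_N|/√v_E > 1.96, given kept)

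| d (SD) | P(sex dropped in GNE) | False positive if dropped | False positive if kept | Overall |
|---|---|---|---|---|
| 0 | 0.950 | 0.050 | 0.478 | 0.071 |
| 0.1 | 0.871 | 0.102 | 0.287 | 0.126 |
| 0.2 | 0.629 | 0.265 | 0.156 | 0.225 |
| 0.25 | 0.469 | 0.384 | 0.124 | 0.246 |
| 0.3 | 0.314 | 0.515 | 0.109 | 0.236 |
| 0.5 | 0.017 | 0.914 | 0.122 | 0.136 |
| 0.7 | <0.001 | 0.997 | 0.129 | 0.129 |

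For example, at d = 0.25: 0.469 × 0.384 + 0.531 × 0.124 = 0.180 + 0.066 = 0.246. A 20,000-run simulation gave 7.3%, 12.6%, 22.8%, 24.8%, 23.6% and 13.4% at d = 0, 0.1, 0.2, 0.25, 0.3 and 0.5.

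**Sex always kept, two-stage subtraction unchanged.** The true variance of b_E − b_N is v_E + v_N, but the test uses v_E. The effective critical value is 1.96 × √(v_E/(v_E + v_N)) = 1.96 × √(270/450) = 1.518, which gives 12.9% at every d.

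**Joint test.** Dividing b_E − b_N by √(v_E + v_N) gave 4.9% to 5.2% in the simulation at every d examined.

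**Sensitivity.** Participants with 36–39 or more than 70 repeats leave the YTO analysis, so GE may fall below 180; the article does not say by how many. With 150 GE and 270 GNE the peak is 21.4%; with 120 and 180 it is 24.5%.

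**The case against.** **The tests are secondary.** The stated hypotheses concern GE-versus-GNE differences and the effects of repeat length, age or YTO within GE. Keeping sex terms in the GE model when significant can be seen as covariate selection, and the p-value the article interprets is the one for YTO. This stands, and it sets the weight of the point. A reader might infer that the YTO findings or the projected power are also wrong. Nothing here shows that: Table 5 concerns YTO effects, and a sex difference left in the GE values can be picked up and adjusted for by the GE sex test. But the third step does describe its sex test as one for additional differences, and as described it cannot support that meaning.

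**The wording is ambiguous.** The exclusion clause may refer to the interactions only, and the imaging–clinical paragraph suggests that sex is always corrected. On that reading the 22–25% figures do not apply to the main effect. What remains is 13%, from a different cause.

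**The peak depends on d.** The highest rates need a shared sex difference of about 0.2–0.3 SD, and the article gives no sex effect size for any outcome. Where the difference is large, as may be expected for brain volumes, sex is nearly always kept and the rate is 13%. It would be wrong to quote 25% as the rate for every outcome.

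**The article is condensed.** A fuller plan may carry the GNE error forward. If it does, the 13% component disappears, but the problem of dropped terms does not.

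**Interactions were not computed.** The table covers the sex main effect. The same mechanism applies to sex-by-age dropped in GNE and sex-by-YTO tested in GE, but these figures do not give its size.

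**Conclusion.** The point holds for the secondary sex testing. As described, a significant sex term in the GE model does not show that the sex effect differs between GE and GNE.

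With 270 GNE, 180 GE, one effective observation each and an equal true sex effect in both groups, the false-positive rate for an additional sex main effect is about 7% at d = 0, 13% at 0.1 SD, 22–25% at 0.2–0.3 SD and 13% from 0.5 SD, against 5% nominal. If the sex main effect is always kept, it is 13% throughout. Repeat visits and family clustering change the effective sample size but not the mechanism.

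The point also reaches the imaging–clinical models, for any outcome whose sex term was dropped. A reader might conclude that keeping sex in the GNE correction is enough. It is not: within the two-stage subtraction the rate is still 13%, which at d = 0 is worse than the 7% under the plan's rule.

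**What to change.** Test additional sex effects in one mixed model fitted to GE and GNE together: sex-by-group for the main effect, and sex-by-YTO net of the normal sex-by-age effect for the trajectory. Keep sex and sex-by-age in that model whatever their p-values, with the subject and family random effects already planned. State whether the present exclusion sentence covers the sex main effect or only the interactions, and check the reason for omitting sex from the imaging–clinical models against the outcomes for which sex was in fact corrected.

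The cost is one extra model per outcome and a few degrees of freedom. No new data are needed, and the two-stage YTO analysis can otherwise stay as planned.
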